### 2.4. Experimental Devices Utilised

The whole sample will be monitored using Biosignalplus series devices (PLUX Wireless Biosignals S.A., Lisbon—Portugal). Four sensors for detecting heart rate, respiratory rate, skin conductance, and body temperature, designed to collect data continuously and éin real time, will be used. These devices are connected to a 4-channel hub (Biosignalsplux 4-channel hub). The hub uses a Bluetooth Class II connection to communicate with the computer and transmit captured data. The data will be processed by the dedicated OpenSignals software.

Participants in the CBT-VR arm will also wear an Oculus Quest wireless virtual reality (VR) headset. The viewer is managed by a specific application that has been developed with “multiplayer” architecture using the Unreal Engine 4 development tool and that includes an immersive application that is used by the patient through the VR viewer and a desktop application that is used by the therapist, which acts as a server and determines everything the user will see. See Table 4.

Once the application has been started on the desktop, the operator, using a third-party program (Sidequest), controls the start of the application on the user’s display, which will directly receive the data selected by the operator. Furthermore, through Sidequest, the operator will be able to monitor everything the user sees and has the ability to reset the program.

Three different standard work environments have been created: an office, a supermarket, and a mechanic’s shop.

In the first scenario, the character that interacts with the patient is sitting behind a desk with a computer. From a big window in the background, the patient can see other characters walking inside the hall next to the office. The main character wears a formal suit with a tie (or a business suit for the female character). The user’s point of view is collocated in front of the desk in a seated position.

In the second scenario, the environment represents a medium-sized supermarket with some cashiers and shoppers walking between shelves. In the background, the typical sounds of the supermarket can be heard. The character that interacts with the patient is standing in front of the checkout wearing a supermarket uniform over moderately formal clothes (e.g., shirt/tie). The user’s point of view is placed behind the checkout, as if he/she is the cashier during his/her work shift. The third environment is a standard mechanical workshop where a character appears in dirty overalls; in this scenario, the characters (mobber and patient) are simply standing in space facing each other.

The 3D characters can be male and/or female and are selected from a group of 20 model derived from real pictures of the mobbers with the possibility of adding particular features (e.g., beard, haircut). Three body animations have been created for all characters ranging from a rest position (not completely static) to a typical animated argument, both for standing and seated positions. As for the face, there is the possibility to program particular expressions to add emotion and realism to the characters using the universally recognized faces of emotions: happiness, sadness, anger, surprise, and fear, with the possibility of a six expression of “flirt”.

In this way, different working life scenarios can be created with increasing anxiety-provoking intensity.

### 2.5. Procedures, Outcomes, and Adverse Events

Participants will be randomized with a 1:1 ratio for CBT-E or CBT-VR without any specific criteria in order to prevent any randomization bias. Researchers involved in the outcome measures will be blinded to the allocation. Both the CBT training are assumed to be appropriate and beneficial for participants based on evidence from the literature. The training for each individual subject will begin within 7 days from T0, and each patient will perform 8 sessions of CBT-E/CBT-VR distributed 1 every week. If the subject is unable to perform the session on the scheduled day, a new date will be agreed within one week, failing which the patient would be excluded from the study. The intervention will also be discontinued if the participant withdraws consent or if a change in circumstance results in the participant meeting the trial exclusion criteria and becomes unsafe to engage in the intervention, or if any side effects would arise. These participants will remain in the analysis for data collected up until the date of withdrawal. The intervention is individualized, and progression/modification will be determined through discussions with the subject and the other members of the trial team. Every discontinuation will be replaced in order to reach the trial sample size.

The training protocol of CBT-E/CBT-VR is summarized in Table 5.

All outcomes will be performed before, during, and after the intervention phase, which is 10 weeks in total. The first week involves enrollment, randomization, and baseline data; the second to ninth week involves the training program; and the tenth week involves the patient final report. The outcomes measured will be physiological and clinical parameters, as well as their variations/comparison during the two training programs.

In particular, the physiological signs of stress reporting variations of temperature, skin conductance, heart rate, and respiratory rate will be recorded.

Acute psychic events (such as anxious states up to panic attacks or other emotional states of intensity that cannot be tolerated by the subject) or neurovegetative manifestations given using the 3D viewer, such as nausea, dizziness, etc., could occur during the sessions. Finally, there could be minimal traumatisms with objects in the room where the virtual simulation activity will be carried out. Such events could lead to the interruption of exposure, and, in this case, they would be managed clinically by the therapist. Whether to resume the exposure technique will be decided clinically on a case-by-case basis. Any adverse events will be collected in an ad hoc form and notified as required by current legislation.

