The literature has evidenced that “exposure therapy” of CBT (CBT-E) seems to be the most effective technique to manage stress symptoms, including work stress diseases [27]. The overall goal of exposure therapy, according to the American Psychiatric Association, is to “reduce a patient’s fear and decrease avoidance” of a patient to his “feared objects, activities, or situations” using a safe environment [28]. There are many different approaches to exposure therapy, which incorporates relaxation exercises as well as gradual exposure to the feared item or situation which tackles the person’s milder fears first before working on the more difficult tasks. In certain situations, the “flooding technique” of exposure therapy (as opposed to a gradual approach) is used to treat the most difficult or intense fear or phobia, with therapy continuing until that fear or phobia is overcome. In this treatment, patients are not allowed to remove themselves from the situation [29]. The advantage of this approach is that it is quick and usually effective. The practice of flooding, also known as “immersion,” initially produces an anxious response of maximum intensity and, as a consequence of repeated exposure to the phobic stimulus, is subsequently followed by a physiological decrease. In reality, the subject tends to deliberately and consecutively avoid the confrontation with the anxiety-provoking stimulation, thus preventing the extinction of the phobic response. Through the flooding procedure, which is one of the so-called “strong” techniques of CBT, the therapist leads the patient through the experience, on an imaginative or real level, of the situation that scares the patient the most and for as long as possible. Generally, anxiety decreases after reaching a peak or, in some cases, disappears completely [30].

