Davidson Trauma Scale (DTS), self-rating for measuring the frequency and severity of Post-traumatic Stress Disorder (PTSD) symptoms in three clusters: intrusion/avoidance/hyperarousal [13]
Clinical Global Impressions Improvments (CGI-I), to quantify patient progress/treatment response over time [40]

**Table 4 ijerph-20-05735-t004:** Desktop application elements.

Setting selected in the initial menu
Gender of the character selected in the initial menu
Facial expressions selected in real time by keyboard
Body movements selected in real time by keyboard
Sentences in real time spoken by the operator and listened by the user with a voice that changes tone depending on the gender and personality of the character

**Table 5 ijerph-20-05735-t005:** CBT rehabilitation protocol for occupational stress diseases.

*Session 1*	Global evaluation of the patient. Administration of psychometric instruments. Assessment and engagement, including the development of a problem list and establishment of shared goals. Introduction to the principle of exposure therapy: definition and rationale.
*Session 2*	Classification of work stimuli through a Subjective Units of Distress Scale (SUDS: 0 = no anxiety at all; completely calm; 3 = some anxiety, but manageable: 5 = getting tough; wouldn’t want to have it all the time; 7–8 = severe anxiety that interferes with daily life; 10 = worst anxiety you’ve ever felt). Analysis of some sensations high distressed stimuli/situations avoided. Discussion of catastrophic interpretations. Disadvantages resulting from the avoidance and/or application of other dysfunctional behavioral mechanisms.
*Session 3*	Exposure to a neutral scene aimed at setting the exposition in the VR environment or in the imagination. Inter-session tasks: ABC techniques for work-related emotional stimuli. Practice of relaxing exercises.
*Session 4–8*	Exercises of exposure to the maximum phobic work stimuli, at the maximum level of intensity for an extended amount of time (flooding technique) using the VR environment or in imagination alternating with relaxation exercises. Analysis of the emotions felt during the approach to the phobic stimulus with re-elaboration of it and related thoughts. Identification of dysfunctional behaviors linked to it and identification of more functional behaviors.

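### The any-side-effect stopping rule fits badly with case-by-case resumption, and stopped patients are replaced without a T1 value

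*Protocol article*

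**What the plan says.** All the relevant rules are in section 2.5 of the protocol article.

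- **Trigger for stopping.** The intervention is discontinued on withdrawal of consent, on a change that makes the patient meet the exclusion criteria and unsafe to treat, "or if any side effects would arise".
- **Data after stopping.** "These participants will remain in the analysis for data collected up until the date of withdrawal".
- **Replacement.** "Every discontinuation will be replaced in order to reach the trial sample size".
- **Expected events.** The adverse-event paragraph names acute psychic events, minor knocks in the simulation room, and viewer symptoms: "neurovegetative manifestations given using the 3D viewer, such as nausea, dizziness, etc., could occur during the sessions".
- **Handling of those events.** "Such events could lead to the interruption of exposure", with clinical management by the therapist. Then: "Whether to resume the exposure technique will be decided clinically on a case-by-case basis".

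Section 2.2 schedules data at baseline, at every session and at T1, and section 2.5 places the final report in week 10. Section 2.4 gives the headset to the CBT-VR arm only. Table 5 prescribes exposure in both arms in sessions 4 to 8, "at the maximum level of intensity for an extended amount of time (flooding technique) using the VR environment or in imagination".

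**The concern.** Two things are fixed badly, and the second matters more.

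First, the same event can be handled in two ways. Take transient dizziness from the viewer. The stopping sentence ends the programme. The adverse-event paragraph allows a pause and possible resumption. Staff have to choose, and their choice helps to decide who reaches T1.

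Second, the consequences of stopping are themselves written down. A patient whose data end at withdrawal has no T1 value, and a new patient is enrolled to keep the number up. The new patient adds a T1 value but does not supply the one missing from the randomised patient who stopped. If stopping is related to outcome and differs between arms, the T1 comparison of CBT-VR with CBT-E is no longer the comparison that randomisation set up. One cause of stopping, viewer symptoms, exists in only one arm, so a difference in stopping is possible. A later analysis cannot recover T1 values that were never collected.

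**Working it through.** **Comparing the rules**

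| Question | Stopping sentence (2.5) | Adverse-event paragraph (2.5) |
|---|---|---|
| What is affected | the intervention | the exposure |
| Trigger | any side effect | named expected events |
| Action | will be discontinued | could be interrupted |
| Afterwards | data to withdrawal, then replacement | resumption decided case by case |

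The repeated conditional in the stopping sentence makes side effects a separate trigger, so the safety wording attached to the exclusion criteria does not limit it.

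**Which arm each event can stop**

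- Acute psychic events that cannot be tolerated, including panic: either arm, since both receive flooding.
- Viewer nausea or dizziness, and knocks during the virtual simulation: CBT-VR only.

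**Size**

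The plan states no figure for side effects, stopping or its effect on outcome, so there is nothing to reproduce. What follows is an illustration.

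Inputs from section 2.1: 15 patients per arm, a planned difference of 1 CGI point, and a post-treatment SD of 1.07.

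Assumptions, not in the documents:

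- kV CBT-VR and kE CBT-E patients stop, and each is replaced in the same arm.
- Only observed T1 values are compared.
- Stopped patients would have scored d points higher (worse) at T1 than the others, equally in both arms.

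An arm with k stops has 15 + k randomised patients and 15 T1 values. Leaving out the stopped patients lowers the arm mean by d × k/(15 + k). The shift in the arm difference is therefore

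shift = d × [kV/(15 + kV) − kE/(15 + kE)].

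The bracket for three cases:

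- (kV, kE) = (2, 1): 2/17 − 1/16 = 0.118 − 0.0625 = 0.055
- (4, 2): 4/19 − 2/17 = 0.211 − 0.118 = 0.093
- (4, 0): 4/19 = 0.211

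The error rate is the two-sided 5% t-test rejection rate with no true difference (noncentral t, SD 1.07, 28 df). The noncentrality is shift / (1.07 × √(2/15)) = shift / 0.391.

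| (kV, kE) | Shift, d = 0.5 | Error rate, d = 0.5 | Shift, d = 1 | Error rate, d = 1 |
|---|---|---|---|---|
| (2, 1) | 0.03 | 0.0505 | 0.06 | 0.052 |
| (4, 2) | 0.05 | 0.0515 | 0.09 | 0.056 |
| (4, 0) | 0.11 | 0.058 | 0.21 | 0.082 |

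The shift is 0 when d = 0 or kV = kE, and its sign reverses if CBT-E loses more patients or if d is negative.

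The document does not say which arm a replacement enters. In the extreme case where four CBT-VR patients stop, none in CBT-E, and all four replacements fall in CBT-E, there are 11 and 19 T1 values. The share is 4/15 = 0.267, so d = 1 gives a shift of 0.27 points and an error rate of 0.097. At d = 0.5 these are 0.13 and 0.062.

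**The case against.** **The two paragraphs may govern different things.** One concerns the eight-session intervention, the other the exposure technique within a session. On that reading, an event pauses exposure and only a serious problem ends the programme. Section 2.5 also calls the intervention individualised, with modifications settled by discussion. This is a fair reading and it weakens the contradiction. But the text does not say it, and the word any in the stopping sentence points the other way.

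**Ordinary flooding anxiety.** A reader might infer that the expected anxiety peak is itself a stopping event, because section 1.1 says flooding "initially produces an anxious response of maximum intensity". The documents do not support this. Section 1.1 describes the peak as how the technique works, followed by a decrease, and nowhere calls it a side effect. The adverse-event paragraph ties psychic events to an intensity that the patient cannot tolerate.

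**Stopped patients are not discarded.** The text says they remain in the analysis, so it would go too far to say that replacements take their place. How partial data enter the comparison may also be settled in an analysis plan that is not shown. That stands, but whether a T1 assessment takes place is a matter of conduct, and the article limits the data to the date of withdrawal.

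**The illustration does not isolate the wording clash.** This is correct. It measures missing T1 values with replacement, which would arise under any stopping threshold. Rewording the trigger alone would not remove them, so the fix needs two parts.

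**A condensed article may omit severity grades.** This is true, and the missing grade is not the point. The point is that the rule the article does state is hard to reconcile with the paragraph after it.

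**Conclusion.** The point holds in a limited form. The stopping sentence and the adverse-event paragraph fit badly together, though a within-session reading could reconcile them. The firmer defect is that stopped patients, as the rules are written, have no T1 value while replacements restore the sample size but not the randomised comparison.

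Viewer symptoms are a cause of stopping found only in CBT-VR, so stopping may differ between arms. A reader might infer that this favours CBT-VR. The documents do not support any direction: CBT-E patients can also stop, and nothing links stopping to outcome.

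The size is unknown and may be zero. With same-arm replacement and d up to 1, the cases tabulated give shifts of at most 0.21 points and error rates of at most 0.082. The extreme case, with every replacement in the other arm, reaches 0.27 points and 0.097. These upper values need four stops in CBT-VR, none in CBT-E, and a d as large as the whole planned difference. All of these are assumptions. The change is worth making because it is cheap and has to be made before T1 data are lost.

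**What to change.** 1. Replace the any-side-effect trigger in section 2.5 with one rule for both arms that agrees with the adverse-event paragraph: pause exposure when an event occurs, and discontinue the intervention only if the clinician judges the event intolerable or unsafe.
2. Perform the scheduled T1 assessment in every randomised patient who stops, unless consent is withdrawn. Keep these patients in the arm comparison as randomised, even if a replacement is enrolled.

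The cost is one or two protocol sentences and a few T1 visits in patients who would otherwise not have had one. Including patients who stopped may make the observed effect smaller.

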### 2.6. Data Collection, Management, Statistical Method, and Ethical Considerations

The collection of the data will be performed in paper and later entered electronically. All data will be confidential. Enrolled patients will be registered in anonymous form using an identification code (progressive number), which will be used for data management solely for research purposes. The recorded data will be anonymized to avoid any link with patients. The data will be archived in an Excel program and kept at the trial sites under the responsibility of the principal investigator. Access to the data will be allowed only to personnel directly involved in the research protocol and protected by a password. Patients will not be identified by name in future publications. Participants will be informed about all main aspects of the research and of their right to refuse to take part or to withdraw consent to participation at any moment. An insurance policy to protect the subjects participating in the trial will be stipulated with the insurance company selected by the University of Pisa.

The data will be recorded in a specifically designed database and elaborated by means of the SPSS software (version 26). The Kolmogorov–Smirnov test will be used to examine variables for normal (Gaussian) distribution. Therefore, the comparisons between patients’ groups for variables of non-Gaussian distribution will be performed by means of non-parametric statistical tests; in particular, the Mann–Whitney test for independent samples will be used. The Student’s t-test for independent samples will be used to compare groups for variables of Gaussian distribution. According to non-Gaussian or Gaussian distribution of paired data, the Wilcoxon test and the Friedman test or the Student’s t-test for dependent samples and the repeated measures ANOVA will be used, respectively. The chi-square test will be used to compare the frequencies of categorical variables. Correlations between continuous variables will be examined by means of Spearman’s coefficient in case of non-Gaussian distribution or by means of Pearson’s coefficient in case of Gaussian distribution. A regression analysis will be used to explore the relationship between more variables. A *p* value less than 0.05 will be considered significant.

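### Discontinued patients are replaced and no end-of-training assessment is provided for them, so the T1 and last-session comparisons are made among completers and replacements, not all randomised patients

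*Protocol article*

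**What the plan says.** Four rules in section 2.5 of the protocol article act together.

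- **Missed session.** If a session cannot be held as scheduled, "a new date will be agreed within one week, failing which the patient would be excluded from the study".
- **Stopping the intervention.** It ends on withdrawal of consent, when a change in circumstances means the patient meets the exclusion criteria and "becomes unsafe to engage in the intervention, or if any side effects would arise".
- **Data kept.** "These participants will remain in the analysis for data collected up until the date of withdrawal".
- **Replacement.** "Every discontinuation will be replaced in order to reach the trial sample size".

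The same section names a risk tied to the headset: "neurovegetative manifestations given using the 3D viewer, such as nausea, dizziness, etc., could occur during the sessions". The sentence containing it also lists acute psychic events, up to panic attacks, which are not tied to the headset. On what follows such an event it says: "Whether to resume the exposure technique will be decided clinically on a case-by-case basis".

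Section 2.6 compares groups by the independent-samples t-test or Mann–Whitney test. For paired data it names Wilcoxon and Friedman tests or, for Gaussian data, the t-test "for dependent samples and the repeated measures ANOVA will be used, respectively". Section 1.2 (Hypothesis 2) predicts a greater reduction in physiological parameters in the last session with CBT-VR. Section 2.1 calls the study a superiority trial of 30 patients, 15 per arm.

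**The concern.** The plan does not separate stopping the sessions from leaving the study. For a patient who stops, the last data point is the date of stopping; no later assessment is described, and a new patient is enrolled. If this is followed as written, T1 and last-session values exist only for patients who completed their own arm's programme, some of whom will be replacements.

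Randomisation makes the groups that were randomised comparable. It does not do so for the subgroups that completed. If the two programmes lose different kinds of patient, the T1 difference mixes treatment effect with selection. The aim in sections 1.1 and 3 is a rehabilitation programme to be offered to workers, so the result of most use is the effect in all who are offered it. That result would not be available. The pre-to-post change predicted in Hypothesis 1 is affected in the same way, because the paired tests need a T1 value.

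**Working it through.** **1. Which data survive for a patient who stops**

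| Comparison | Values needed | Discontinued patient |
|---|---|---|
| First-session physiology (Hypothesis 2) | early-session value | included |
| Last-session physiology (Hypothesis 2) | last-session value | absent |
| Between-arm test at T1 | T1 value | absent |
| Paired t-test or Wilcoxon, T0 to T1 | both values | absent |
| Friedman or repeated-measures ANOVA | full series | absent |

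Retaining data up to withdrawal is therefore honoured for early sessions but not for the end-of-training comparisons.

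**2. The protocol's own sample size**

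Inputs from section 2.1: difference 1 CGI point, 95% confidence, 90% power, 1:1 allocation, SDs 0.74 (pre) and 1.07 (post).

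- Normal approximation, SD 0.74: n = 2 × (1.960 + 1.282)² × 0.74² / 1² = 11.5, so 12 per arm.
- Exact t-based calculation, SD 0.74: 13 per arm (power 0.911), total 26. The stated figure reproduces.
- SD 1.07 gives 25 to 26 per arm and does not reproduce it. That is a separate matter.
- Margin: 30 − 26 = 4 patients, and 4/30 = 13.3%.

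**3. How many could be excluded for sessions not made up**

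The documents give no rate. Assume each of the 8 sessions independently has probability q of not being made up within a week. The proportion excluded is 1 − (1 − q)^8.

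- q = 1%: 1 − 0.99^8 = 7.7%
- q = 3%: 1 − 0.97^8 = 21.6%
- q = 5%: 1 − 0.95^8 = 33.7%

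**4. Size of the shift in the arm difference**

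Let p be the proportion stopping in an arm and δ how much worse those patients would have ended than that arm's completers. The completers' mean is then too favourable by p × δ, and the arm difference shifts by p_VR × δ_VR − p_E × δ_E.

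- p_VR = 0.20, p_E = 0.05, δ = 1 in both (all assumed): 0.20 − 0.05 = 0.15 CGI point towards VR, or 15% of the 1-point target.
- Equal p and equal δ: 0.
- δ = 0: 0, whatever the rates.
- Rates the other way round: 0.15 point towards CBT-E.

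The standard error of the difference with 15 per arm is SD × √(2/15), which is 0.27 (SD 0.74) to 0.39 (SD 1.07). The 0.15 shift is 0.4 to 0.55 of a standard error.

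**5. Simulation check**

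Setting: no true effect, 15 completers per arm, SD 1.07. Stopping depends on a latent score that has correlation ρ with a poor outcome. Negative values favour VR.

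| Dropout VR / CBT-E | ρ = 0 | ρ = 0.3 | ρ = 0.5 | ρ = 0.8 |
|---|---|---|---|---|
| 20% / 20% | 0.00 | 0.00 | 0.00 | 0.00 |
| 20% / 5% | 0.00 | −0.08 | −0.13 | −0.21 |
| 30% / 5% | 0.00 | −0.12 | −0.21 | −0.33 |

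For ρ from 0.3 to 0.8, the chance of a false finding in favour of VR rises from a nominal 2.5% to 4–8% in the second row and 5–15% in the third. With SD 0.74 the shifts are about 30% smaller.

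**The case against.** The strongest reply is that an unseen full protocol or analysis plan may handle missing data, and that section 2.6 nowhere says incomplete cases are dropped. That is fair for the choice of method. It does not answer the main point, because no later analysis can recover T1 values that were not collected, and section 2.5 itself sets the end of data collection and the replacement rule.

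Several stronger readings are tempting, and the documents do not support them.

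- **That replacement itself creates the bias, or that replacements are chosen for completing.** A replacement enters under the same rules and may also stop. The bias comes from the missing T1 values; replacement only restores the count. Deleting the replacement sentence alone would not cure it.
- **That discontinued patients vanish from the analysis.** Their data up to stopping are kept, so retained patients plus replacements may exceed 30.
- **That one missed session removes a patient.** Only failure to hold it on the rebooked date does.
- **That poor responders are swapped out.** No discontinuation for lack of efficacy is listed, although withdrawal of consent could reflect it.
- **That the bias favours VR.** Headset nausea and dizziness are one route specific to the VR arm. Acute psychic events can occur in either arm, since both use flooding in sessions 4–8 (Table 5). Table 2 lists vestibular, neurological and ocular disorders among its exclusions, which should limit headset intolerance. Nausea also need not predict a poor CGI result.

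**Conclusion.** The point stands as something that should be fixed. As written, section 2.5 leads to T1 and last-session comparisons among completers and replacements, and the effect in all randomised patients is not estimated. That follows from the text, on the natural reading that a patient excluded or withdrawn has no T1 visit; the article does not say so outright for those stopped for side effects.

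The size and direction of any bias are not established. The 0.15-point illustration rests entirely on assumed rates (20% and 5%) and an assumed 1-point penalty. The simulation puts the same rates at 0.08 to 0.21 point when stopping is moderately to strongly related to outcome, and at zero when it is unrelated or has the same rate and relation to outcome in both arms.

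Two pairs of statements also conflict. Excluding patients from the study sits beside keeping them in the analysis, and it is unclear whether the latter covers those excluded for a missed session. Stopping for any side effect sits beside case-by-case resumption.

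**What to change.** **Section 2.5**

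- Separate stopping sessions from leaving the study. Collect the T1 battery at week 10 from every randomised patient who has not withdrawn consent to data collection, however many sessions were attended.
- Remove the replacement rule, or at least state that replacements do not displace the patients originally randomised.
- State that all randomised patients are analysed in their assigned arm, and report discontinuations by arm with reasons.
- Reconcile exclusion from the study with remaining in the analysis, and stopping for any side effect with case-by-case resumption. The clinical rule itself is for the sponsor to decide.

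**Section 2.6**

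- For repeatedly measured continuous outcomes, use a likelihood-based mixed model in place of repeated-measures ANOVA, so that partial series contribute.
- CGI-I rates change from baseline (section 2.3) and so has no T0 value. Compare arms at T1 without a baseline CGI-I covariate, and keep a rank-based analysis for ordinal outcomes.
- Show completers as a sensitivity analysis.

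**Cost.** A T1 visit for patients who stop early, and changes of wording. Some T1 values may still be missing. Thirty patients leave room for 4 losses (13%) against the protocol's own 26, although the article does not present those 4 as a dropout allowance. Larger losses would reduce precision: at 21.6% without T1, 30 × 0.784 = 23.5 patients would remain. The stated power should then be restated, or the number randomised raised. For example, 26/0.80 = 32.5 means 33 patients, or 34 for equal arms, at an assumed 20% loss.
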